A systematic review and meta-analysis on suicide rates after discharge examined publications from 1946 to 2016. Altogether, 100 studies were analysed that included 17,857 suicides. The pooled suicide rate was 484 suicides per 100,000 person-years (95% CI = 422–555). The suicide rate was highest within 3 months after discharge (1132; 95% CI = 874–1467). In the period from 3 months to 1 year, suicide rates were 654, 494 in the period after year 1 to year 5 and 366 for the follow-up period of 5 to 10 years, and 277 for studies with follow-up periods longer than 10 years [12].

A review on suicide rates following hospital discharge examined 48 studies from 1964 to 2017. The pooled annualised suicide rate was 241 (95% CI = 238–243) per 100,000 person-years including 41 studies [13].

Several causes of this excessively increased suicide risk in the months after discharge may be considered as follows:
Patients were not treated successfully. There was treatment failure or only a partial response to treatment.New or different problems developed after discharge that overburdened the individuals’ potentially reduced coping strategies.Because of other reasons, clinical symptoms worsened, for example, due to a lack of adherence to medication.The influence of the therapeutic relationship—usually ending with discharge. To date, there have been only a few studies and statistically reliable results. One study analysing German railway suicides showed an odds ratio of 22.86 for the change of therapist during the hospital stay and the association with suicide [14].Other causes such as disappointment and hopelessness after failing the highest level of care, the associated stigma of being admitted to a mental health facility, being in contact with patients that are potentially very sick, and learning about other more lethal methods of suicide.

The group of patients being discharged from a psychiatric inpatient stay represents a population at risk for suicide that does not receive specialised care regardless of the type of mental disorder. Specific care concepts focussing on these patients with tremendously increased suicide risk rarely exist.

Moreover, systematic investigations on the complex and heterogeneous background of increased suicide mortality after discharge from psychiatric hospitals and the influences of different treatment settings on suicide prevention were not carried out.

For this reason, the presented study examines the following questions:

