### Course

All patients receive a baseline visit (V0) during the week prior to discharge. At the baseline visit, data on demographics, substance use, psychiatric and medical history and treatment, history of suicidality, and family history of suicidality are documented.

In group 1, study contacts are scheduled at 6 (V6), at 12 (V12), and at 18 (V18) months after discharge from the psychiatric hospital. In group 2, more frequent study contacts are organised: During a period of 6 months after discharge, study visits are scheduled monthly (V1–V6), and subsequently every 2 months during the next period of 6 to 18 months after discharge (V8–V18). There will be a total of 3 study visits in group 1 and 12 study visits in group 2. The protocol (Fig. 1) accepts flexibility in terms of time, plus/minus 1 week, for study visits in the first 6 months after discharge, as well as a plus/minus 2 weeks tolerance for study visits V8 to V18. In case a patient gets admitted to a hospital while participating in the study, the course will be continued as conducted. Study visits include an evaluation of events that occurred between the study visits, e.g., stress-related events, inability to work, days of inpatient treatment, change or discontinuation of any treatment, and change of doctors, or therapists. Both baseline and study visit additionally includes several assessments recording symptomatology described in the next section.

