#### Patient-administered scales

The self-rating version of S-STS will be used as a self-rating instrument on suicidality. The Visual Analogue Mood Scale (VAMS) [18] will be used to reflect the current subjective mental state. Both will be applied at baseline contact and at each following contact in both groups. At the baseline visit only (V0), patients of both groups will be asked to complete a questionnaire on perfectionism [21–24], as well as the FPI-R Questionnaire (Freiburger Persönlichkeitsinventar, [25]) to investigate whether and to what extent various psychological constructs (e.g., perfectionism, aggressiveness) are associated with suicidality. Additionally, we ask patients to fill out the Resilience Scale (RS13) [26] to investigate possible influences on the development of suicidality. The RS13 measures resilience on a 7-point scale and is the short German version of the RS-25 from Wagnild and Young [27].

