#### Secondary outcome measures

Group comparisons of secondary outcome measures will be conducted using analysis of (co)variance (AN(C)OVA), Poisson regression, logistic regression, *t* tests, Chi-square tests, or non-parametric methods as appropriate. The course of suicidality measured with S-STS, as well as scores of the other scales, will be analysed within groups using repeated measures AN(C)OVA for both groups separately comparing baseline values with scores at 6, 12, and 18 months.

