The present study has several limitations. First, patients with a principal diagnosis of only categories F2 and F3 of ICD-10 (schizophrenia, schizotypal or delusional disorders, depression, bipolar disorder) will be included. In contrast, all other diagnoses will be accepted as comorbidities only. This procedure leaves out several groups of patients. We tried to restrict the heterogeneity of our study population in favour of receiving insights that are more meaningful for a well-defined group of patients at this first step of approaching very critical aspects of suicidality. Second, a bias may arise from the fact that patients have a choice of which group they would like to be placed in, either group 1 or group 2. On the other hand, this choice can offer useful insights into real-world clinical aspects by reflecting patients’ different characteristics as well as needs and motivation to make use of suicide prevention measures providing personal contact. This is in line with the ethical requirements of not withholding any condition from participants.

As a limitation of our study, we do not examine developments during the first days after discharge. The first study contact is scheduled 1 month after discharge. A recently published meta-analysis comprising 34 publications showed a pooled estimate of the suicide rate of 2950 suicides per 100,000 person-years (95% CI = 1740–5000) [28]. The pooled estimate of the suicide rate during the first month after discharge was 2060 per 100,000 person-years (95% CI = 1300–3280).

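### The within-group course analysis is fixed at baseline and months 6, 12 and 18, so group 2's scale scores from 9 of its 12 follow-up visits, including all five before month 6, enter no named analysis

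*Protocol article*

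**What the plan says.** The Protocol article, Secondary outcome measures, states that the course of the S-STS and of the remaining instruments "will be analysed within groups using repeated measures AN(C)OVA for both groups separately". The same sentence fixes the times to be contrasted: "comparing baseline values with scores at 6, 12, and 18 months". Methods/design gives the same three follow-up times for the primary endpoint and for the scale-based secondary endpoints.

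The Course section sets different schedules for the two groups. For group 1: "In group 1, study contacts are scheduled at 6 (V6), at 12 (V12), and at 18 (V18) months after discharge". For group 2, in the first half year, "study visits are scheduled monthly (V1–V6"). After that the interval lengthens: "subsequently every 2 months during the next period of 6 to 18 months after discharge (V8–V18"). It gives totals of 3 and 12 study visits.

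On what is collected, the Patient-administered scales section says of the self-rated S-STS and the VAMS: "Both will be applied at baseline contact and at each following contact in both groups". For the clinician-rated scales there is only the general sentence in Course that baseline and study visits include several symptom assessments.

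On timing, the Background reports from a meta-analysis: "The suicide rate was highest within 3 months after discharge". The Discussion, where it sets out limitations, says: "The first study contact is scheduled 1 month after discharge".

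**The concern.** The first study question asks what influences suicide mortality in the months after discharge, and Methods/design lists the identification of such factors as the first objective. Group 2 is the only group with repeated scale scores in the first half year. The one analysis in the article that describes how scores move over time keeps only the visits that group 2 shares with group 1.

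The between-group comparison has to use the common visits. The course analysis does not, because it is run in each group separately. A contrast of baseline with month 6 cannot show whether suicidality rose and fell again in between, and that early pattern is what group 2's monthly visits could reveal.

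The Discussion limitation has a related fault. It concedes only that the first days after discharge are not examined, and supports this with a first contact at 1 month. For group 1 the first contact is at month 6.

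**Working it through.** The check is a count of visits. The article reports no power or sample size calculation, and none is needed here.

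**Inputs** (Course; Secondary outcome measures)
- Group 1 follow-up: months 6, 12, 18.
- Group 2 follow-up: monthly, V1 to V6; then every 2 months, V8 to V18.
- Times in the course analysis: baseline, 6, 12, 18 months.

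**Reproducing the stated totals**
- Group 1: {6, 12, 18} = 3 visits. The article says 3.
- Group 2: {1, 2, 3, 4, 5, 6} + {8, 10, 12, 14, 16, 18} = 6 + 6 = 12 visits. The article says 12.

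**Visits outside the course analysis, group 2**
- {1, 2, 3, 4, 5, 6, 8, 10, 12, 14, 16, 18} minus {6, 12, 18} = {1, 2, 3, 4, 5, 8, 10, 14, 16}.
- That is 12 − 3 = 9 visits, and 9/12 = 75%.
- Before month 6: V1 to V5, five of five. After month 6: V8, V10, V14 and V16, four.
- Group 1: 3 − 3 = 0 visits left out.

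**Time points available to the course analysis, with baseline**
- Group 2 as planned: 1 + 3 = 4. With all scheduled visits: 1 + 12 = 13.
- Group 1: 1 + 3 = 4 either way.

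**Does another named analysis use these scores?**
- Primary outcome measures: an ANCOVA of the clinician-rated S-STS, with the endpoint defined at 6, 12 and 18 months. No.
- Secondary group comparisons: the scale-based endpoints are defined at the same three times. No. Event-type outcomes have no stated times and can draw on the whole follow-up.
- Statistical analysis, explanatory variables: correlations and descriptive summaries for suicidality in the weeks and months after discharge. No visits are named, so use is possible but not stated. No repeated-measures or time-ordered method is given.

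**What is certain about collection.** The self-rated S-STS and the VAMS are stated for every contact. Collection of the clinician-rated S-STS, MADRS and BPRS at interim visits follows only from the general sentence in Course.

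**The case against.** The strongest reply is that the grid is coherent. The endpoints are defined at 6, 12 and 18 months, and a common grid lets the two courses be read side by side. Group 2's extra contacts are also the setting of care under test, not only measurement occasions, and a condensed article may leave further exploratory models to an analysis plan. This justifies keeping the three common times for comparing the groups. It does not explain why the separate analysis of group 2 stops there, and that restriction is stated in the article, not left open.

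Stronger readings are tempting, and the document does not support them:
- *The interim data are collected and never used.* A reader might infer this from the course analysis alone. The explanatory-variable analysis names no visits, and its reference to weeks after discharge fits interim data better than a 6-month grid. What can be said is that no named analysis of scale scores uses them.
- *Everything from the first five months is lost.* Suicide attempts are asked about at every visit, and each visit records events, inpatient days and treatment changes since the previous one. These can enter the event-type analyses. The gap concerns scale scores.
- *The groups cannot be compared at all before month 6.* Group 1's V6 covers attempts and events since discharge, retrospectively. Only its scale scores are missing for that period.
- *The share of suicides falling in the early months measures the loss.* The Background rates concern completed suicides, whereas the omitted data are scores. Using the scores would recover no suicides.

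On the Discussion sentence, it can fairly be said that 1 month is the trial's earliest follow-up contact and that group 1's month-6 start is stated plainly elsewhere. That makes it a small correction, but as a description of the trial's limits the sentence holds for one group only.

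**Conclusion.** The point holds for scale scores in the named course analysis. In group 2, 9 of 12 follow-up visits (75%), including all five before month 6, contribute no scores to any named analysis. The restriction is not needed, because each group is analysed separately. It weakens the description of suicidality in the early months, which the first study question addresses. It does not affect the primary comparison or any other between-group comparison at 6, 12 and 18 months.

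The conclusion assumes that scores are taken at interim visits. This is explicit for the self-rated S-STS and the VAMS, and inferred for the clinician-rated scales. It also assumes that the unspecified correlations are no substitute for a longitudinal analysis, even if they draw on interim visits. The effect on precision cannot be given: patients choose their group, so group 2's size is unknown, and the article gives no variance for the scores. The change is worth making because it is cheap and serves the first objective.

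**What to change.** 1. **Secondary outcome measures:** analyse group 2's course of the S-STS and the other scales with a linear mixed model on all scheduled visits, V0 to V18 (13 time points). Keep months 6, 12 and 18 for the group comparison and for setting the two courses side by side.
2. **First study question, exploratory:** in group 2, relate events and treatment changes reported at a visit to later S-STS, adjusted for the earlier score. Events reported at a visit already precede it, so some time order exists; the adjustment for the earlier score makes it usable.
3. **Interpretation:** state that early-course results apply to group 2 only, which is self-selected and receives the contacts under study. They are not evidence of an effect of the contacts.
4. **Assessments:** say explicitly whether the clinician-rated scales are applied at the interim visits.
5. **Discussion, limitations:** state that the 1-month first contact holds for group 2 only, and that group 1 has no scale scores between baseline and month 6.

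The cost is some extra exploratory analysis of data already scheduled for collection, plus a few sentences of text. No visit, assessment or patient is added.

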### Data and safety management

The study protocol conforms to GCP (Good Clinical Practice) standard procedures, and all investigators participated in GCP courses. Monitor visits are carried out by the staff of the University Hospital Carl Gustav Carus. Study data will be stored for 10 years and will be destroyed afterwards. As per protocol, all serious adverse events will be documented and sent to the sponsor. Very experienced and trained investigators perform the assessments. They took part in mandatory interrater training.

### Ethical considerations

Research on suicide has to consider specific requirements and demands concerning study protocols, study designs, and methodological concepts. All psychiatric patients participating in this study undergo regular available treatment (treatment as usual, TAU). While participation in any of both study groups includes additional contacts to study investigators, a four eyes principle is introduced to meet the particular requirements of care psychiatric patients might need after discharge from the hospital. Participants of both groups agree that in case of significant events (e.g., suicide attempt, suicide), the study investigator is allowed to contact the person the patient chose in advance. The Ethics Committees have approved the study.

## Discussion

As suicide risk in psychiatric patients is highly increased in the period after discharge from a psychiatric hospital, there is a high need to understand the complex phenomenon of suicidality after discharge. To date, however, this high-risk group for suicide has rarely been approached by research. Considering this, the proposed multi-centre pilot study will collect various and heterogeneous data on patients after discharge from psychiatric hospitals, while at the same time offering patients a personal contact setting in the period following hospital treatment, which includes the option to connect with a doctor or therapist. The results of this pilot study should contribute to identifying factors that raise suicide risk after discharge as well as indicate whether a contact setting may be a promising prospect in terms of suicide prevention.

The approach of this study aims at being in accordance with clinical reality, which is essential for a possible future transformation of our results into everyday clinical practice. Being a multi-centre study, the trial population is more heterogeneous, meaning more information is expected to be gained, and more patients can be included.

Several other aspects may play a role within this selected care approach. Study visits will occur in addition to regular care, which means one more social contact independent of the content, which might be especially relevant for isolated patients. Moreover, this increases the chance of recognising suicidal tendencies and prevents them (4 eyes principle). The study appointments establish a link between the end of inpatient treatment and further outpatient care. Some patients may feel less of a break in their relationship due to the familiar environment. Another difference is that the study visits are conducted as safety-focused contacts, which also means that it is possible to have more time for the patient than a regular medical contact would be able to offer. In the case of elevated suicide risk, it is possible to discuss the following procedure within an interdisciplinary team, either within the hospital but also within the study team. Within the study visit, a semi-standardised conversation flow is used. The patients can better adjust to appointments and reflect on their development. There also may be more openness in the conversation. The expectations of the study staff are different from regular doctor or therapist appointments.

The present study has several limitations. First, patients with a principal diagnosis of only categories F2 and F3 of ICD-10 (schizophrenia, schizotypal or delusional disorders, depression, bipolar disorder) will be included. In contrast, all other diagnoses will be accepted as comorbidities only. This procedure leaves out several groups of patients. We tried to restrict the heterogeneity of our study population in favour of receiving insights that are more meaningful for a well-defined group of patients at this first step of approaching very critical aspects of suicidality. Second, a bias may arise from the fact that patients have a choice of which group they would like to be placed in, either group 1 or group 2. On the other hand, this choice can offer useful insights into real-world clinical aspects by reflecting patients’ different characteristics as well as needs and motivation to make use of suicide prevention measures providing personal contact. This is in line with the ethical requirements of not withholding any condition from participants.

As a limitation of our study, we do not examine developments during the first days after discharge. The first study contact is scheduled 1 month after discharge. A recently published meta-analysis comprising 34 publications showed a pooled estimate of the suicide rate of 2950 suicides per 100,000 person-years (95% CI = 1740–5000) [28]. The pooled estimate of the suicide rate during the first month after discharge was 2060 per 100,000 person-years (95% CI = 1300–3280).

## Conclusions

The proposed pilot study will provide insights into the causes of the highly elevated risk of suicide in the period after discharge from a psychiatric hospital. It may point out further research questions and crucial features of suicide prevention procedures.

## Data Availability

Not applicable yet

## Abbreviations

WHO: World Health Organization
NaSPro: Nationales Suizidpräventionsgprogamm (National Suicide Prevention Program)
DGS: Deutsche Gesellschaft für Suizidprävention (German Association for Suicide Prevention)
UK: United Kingdom
SMR: Standardised mortality ratio
CI: Confidence interval
ICD: International Classification of Diseases
S-STS: Sheehan Suicidality Tracking Scale
MADRS: Montgomery Asberg Depression Scale
BPRS: Brief Psychiatry Rating Scale
VAMS: Visual Analogue Mood Scale
AMDP: Arbeitsgemeinschaft für Methodik und Dokumentation in der Psychiatrie
FPI-R: Freiburger Persönlichkeitsinventar
RS13: Resilience Scale
IBM: International Business Machines Corporation
SPPS: Statistical Package for the Social Sciences
ANCOVA: Analysis of covariance
GCP: Good Clinical Practice
TAU: Treatment as usual
